##### **5.4.1 Safety**

Many years of experience with *L. rhamnosus* and *L. reuteri* has shown their safety as an ingredient in food and food supplements and this has been tested in numerous clinical studies in doses up to at least  $10 \times 10^9$  CFU/day without giving rise to any safety concerns. Use of *L. rhamnosus* in general and GR-1® and RC-14® specifically is concluded to be safe in pregnant and lactating women.

### **5.4.2 Contraindications**

GR-1® and RC-14® should not be given to subjects with intolerance towards lactobacilli or any of the excipients used in the formulation.

### **5.4.3 Warnings and Precautions for Use**

The product may contain trace of milk. The product should be used with caution in severely ill and/or immunocompromised patients. Medical help should be sought in case of unfamiliar vaginal odour, discharge or pain.

### **5.4.4 Clinical Studies**

GR-1® and RC-14® as an oral capsule product or in a vaginal capsule formulation have been used in several clinical trials for various different indications. Although none of the studies were designed as safety trials, the overall reporting of AEs was low.

One study randomized 125 Black-African women with Nugent Score 7-10 to either GR-1® and RC-14® or placebo for 30 days. All subjects were given metronidazole 1 g daily for the first seven days of the intervention. Forty-three of 49 subjects (88%) in the probiotic group had normal Nugent Scores and negative sialidase results (an enzymatic test used by some to diagnose BV) compared to 23 of 57 subjects (40%) in the antibiotic/placebo group ( $p > 0.001$ ). This study was subject to a risk of attrition bias as 16 out of 65 in the antibiotic/probiotic group were lost to follow-up compared to 3 out of 60 in the placebo/antibiotic group with no intention-to-treat analysis performed.

Sixty-four Brazilian women with BV (Nugent Score 7-10) were randomized to either GR-1® and RC-14® or placebo for 28 days. All women were given a single dose of tinidazole 2 g. Cure was defined as relief of BV signs according to Amsel's criteria and change in Nugent Score. After 28 days of intervention, 4 out of 32 (12.5%) in the probiotic/antibiotic groups had positive Amsel test, compared to 16 out of 32 (50%) in the placebo/antibiotic group. Moreover, 75% of the probiotic/antibiotic group had a Nugent Score 0-3 compared to 34.4% in the placebo/antibiotic group ( $p = 0.011$ ) at the end of the treatment period.

Hummelen and co-workers investigated long-term efficacy by randomizing 65 Black-African women who were HIV positive and had Nugent Score 4-10 to receive metronidazole 800 mg daily for 10 days and either GR-1® and RC-14® or placebo for 25 weeks. Primary efficacy endpoint was BV cure rate after two weeks treatment in women with Nugent Scores 7-10 at baseline. Secondary endpoints were recurrence rate of BV at 25 weeks, and prevention of BV in women with Nugent Scores 4-7 (asymptomatic BV) at baseline. For the analysis of data, subjects were grouped according to Nugent Scores. After two weeks, women who had BV (Nugent Score 7-10) at baseline 40% in the probiotic/antibiotic group were cured compared to 55% in the placebo/antibiotic group ( $p = 0.3$ ). After 15 weeks there was a trend for higher prevalence of normal Nugent Score among the probiotic/antibiotic group (9 out of 17=53%) compared to the placebo/antibiotic group (5 out of 20=25%) ( $p = 0.08$ ), however, no statistical significant difference was found between the two groups at any time-point. The study suffered from risk of attrition bias, since 14 out of 65 randomized subjects did not complete the study.

In ten (10) clinical trials where a total of 341 healthy subjects were enrolled, four (4) cases of headache were reported and 2 cases of increased appetite. In a study by Anukam et al, 39 subjects received oral capsules of GR-1® and RC-14®, of which a few subjects reported a

single episode of headache and nausea. The most commonly reported AE was headache, which was evaluated to be unrelated to ingestion of the study product.

In three (3) clinical trials investigating the effect of GR-1® and RC-14® in women without clinical symptoms of BV, including one study in women with HIV, 71 subjects were enrolled, seven (7) subjects reported GI AEs and one (1) case of an unspecified vaginal AE. All events were rated mild and the rate and incidence were similar to the placebo group.

#### **5.4.5 Interactions with Medicinal Products**

Lactobacilli are sensitive to numerous antimicrobial products, and concomitant therapy (local and/or systemic) can lead to a decrease in efficacy. Lactobacilli are generally resistant to nitroimidazole antibiotics (such as metronidazole), which is commonly used to treat BV. There are no known interactions between probiotics and other medicinal products.

#### **5.4.6 Overdose**

No overdose with GR-1® and RC-14® has been reported. The human gut contains approximately  $1 \times 10^{12}$  CFU of bacteria/gram faeces and thus an overgrowth based on capsules containing  $1-5 \times 10^9$  seems an unlikely scenario. High doses of a *Lactobacillus* product ( $1 \times 10^{11}$  CFU per day) have been reported to be well-tolerated. This corresponds to 50-100 capsules of this investigational product.

## **6 STUDY DESIGN**

The study population will consist of post-menopausal subjects presenting with intermediate Nugent Scores (4-6). The study duration is 47 days with a final follow-up at 129 days. A total of fourteen (14) subjects will be randomized into this exploratory study.

Subjects will undergo the following treatment phases:

- Two weeks of no treatment (Days 1-15); followed by
- Three days in which each subject randomly receives either two intravaginal placebo capsules or two intravaginal probiotic capsules (Days 16-18) each day; followed by
- 18 day wash-out period; followed by
- Three days in which each subject randomly receives either two intravaginal placebo capsules or two intravaginal probiotic capsules (Days 37-39) each day; and
- Follow-up approximately 90 days after last treatment.

The capsules given on Days 37-39 will not be the same as the capsules given on Days 16-18. During one treatment period the probiotic will be given and during the other treatment period, placebo will be given. Not the subject nor the study staff will know which capsules contain the probiotics.

INHP (placebo or probiotic) consists of capsules to be administered vaginally on study treatment days; once in the morning and once in the evening approximately 12 hours apart.

Following the first two weeks of no treatment, subjects will be given six (6) placebo or probiotic capsules, on Day 15, to be administered vaginally twice daily for 3 consecutive days. Panty liners will be given to use on treatment days. On Day 36, subjects will again be given six (6) placebo or probiotic treatment capsules to be administered vaginally twice daily for

3 consecutive days in the same manner. A diary to track compliance and to rate general vaginal discomfort and record any other adverse events will be given to the patients and reviewed by the study Investigator or designee at the following visit. Subjects that remain colonized with the probiotic strains at Day 47 will return for a follow-up visit on Day 129. During the follow-up phase, all subjects who received treatment will be queried monthly via telephone regarding adverse events on a monthly basis until Day 129. See Section 8 for visit details.

## **6.1 Study Objectives**

### **Primary Objectives:**

The objective of this study is to determine whether *L. rhamnosus* GR-1® and *L. reuteri* RC-14® delivered via capsules to the vagina of post-menopausal women over a three day course of treatment can restore and maintain a lactobacilli-dominated microbiota for one week as measured by:

- A decrease in the Nugent Scores from an intermediate score (4 - 6) at baseline to a normal score (0 - 3) following treatment.

### **Secondary Objectives:**

Determine the effect of *L. rhamnosus* GR-1® and *L. reuteri* RC-14® on the subjects' anti-microbial defences and vaginal comfort as measured by:

- Microbial ecology analysis, human genetic microarrays and multiplex immunological assessments; and
- An increase in symptom relief such as itching, irritation, or general vaginal discomfort.

## **6.2 Exploratory Outcomes**

- Metagenomic study to evaluate whether there is an increased abundance of lactobacilli and decrease in pathogens with probiotic therapy;
- Metabolomic study to determine whether there are differences in the factors associated with improved health between probiotic, placebo, and no treatment conditions;
- Multiplex immunological study to evaluate the modulation of an anti-microbial and/or anti-inflammatory in the host in response to the probiotic;
- Microarray analysis to determine whether there are differences in gene regulation between probiotic, placebo, and no treatment conditions; and
- Symptom analysis to evaluate whether probiotic treatment is associated with symptom relief.

## **6.3 Safety Assessments**

Safety will be assessed through monitoring of physical examination changes and review of adverse events recorded in the subject diary or at the study visits or by telephone.

## **7 SELECTION OF SUBJECTS**

All entry criteria must be met in order for the subject to be entered into the study. Exemptions or waivers to the study criteria will not be granted.

## **7.1 Inclusion and Exclusion Criteria**

### **Inclusion Criteria:**

1. Willing and able to read, understand, and sign the ICF;
2. Post-menopausal female between the ages of 40-80 years old (subject has not had a menstrual period for the past 12 months);
3. Currently in a mutually monogamous sexual relationship or not sexually active;
4. Agree to be sexually abstinent 72 hours prior to each study visit. Also agree to refrain from intercourse for 48 hours after treatment administration;
5. Agree to abstain from the use of any other intravaginal product (i.e. gels, foams, lubricants, douches, etc.) throughout the study period, from the time of screening until Day 47;
6. Willing and capable of following all study instructions; and
7. Good general health.

### **Exclusion Criteria:**

1. Use of vaginal lubricants, or any products applied vaginally within three months prior to *Visit 1* and throughout the duration of study participation;
2. A history or currently undergoing immunosuppressive drug therapy, chemotherapy, or radiation therapy;
3. A medical condition which might compromise their immune system functions (such as cancer, leucopenia, HIV-positive, or organ transplant);
4. Antibiotics and/or antifungal medication use within the last four (4) weeks;
5. Oral probiotic supplement use within 3 months prior to *Visit 1* and throughout the duration of the study;
6. Significant changes in diet during the course of the study.
7. Induced menopause due to surgical or medical interventions, such as bilateral oophorectomy, hysterectomy, chemotherapy and radiation treatment;
8. Currently undergoing local or systemic estrogen therapy who are not willing to alter therapy during the course of the study;
9. A Nugent Score of 0 – 3 or greater than 6;
10. History of drug or alcohol abuse;
11. Currently diagnosed with or being treated for a genital infection or urinary tract infection;
12. Individuals with a sexually transmitted disease (self-reported or detected by the Principal Investigator);
13. At enrollment, have any social or medical condition, or psychiatric illness that, in the opinion of the Investigator, would preclude provision of informed consent, make participation in the study unsafe, complicate interpretation of study outcome data, or otherwise interfere with achieving the study objectives;

14. Participation in a clinical trial involving an investigational product within the past three months; subjects who are currently scheduled to participate in another clinical study concurrently; and
15. Known intolerance or allergy to *L. rhamnosus* GR-1® and *L. reuteri* RC-14® or to any product excipient.

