| Study Design:                                   | 
This is a prospective, randomized, double-blind crossover study.
 
Fourteen (14) post-menopausal women with a Nugent Score of four (4) to six (6) will be included in the study.
 
Subjects will undergo the following treatment phases:
 
 
• Two weeks of no treatment (Days 1-15); followed by
 
• Three days in which each subject randomly receives either two intravaginal placebo capsules or two intravaginal probiotic capsules (Days 16-18) per day; followed by
 
• 18 day wash-out period; followed by
 
• Three days in which each subject randomly receives either two intravaginal placebo capsules or two intravaginal probiotic capsules (Days 37-39) per day.
 
 
The capsules given on Days 37-39 will not be the same as the capsules given on Days 16-18. During one treatment period the probiotic will be given and during the other treatment period, placebo will be given.
 
Both the subjects and the investigator will be blinded as to placebo and probiotic treatments. Subjects will provide vaginal samples on Days 1, 5, 15, 19, 26, 36, 40, and 47. An additional sample may be taken on Day 129 if the subject is still colonized at Day 47.
 
A diary to track compliance and to rate general vaginal discomfort and other adverse events will be given to the subjects on Day 1, Day 15 and Day 36 to be reviewed by the study Investigator or designee at the following visit.
 
Subjects that remain colonized with the probiotic strains at Day 47 will be queried monthly via telephone to monitor for adverse events and have a follow-up visit on Day 129 where a vaginal swab will be taken to determine if they are still colonized by the probiotic strains.
 
Subjects that are not colonized with the probiotic strains at Day 47 will be queried monthly via telephone for adverse events until Day 129. No visit is required at Day 129.
 |

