### **5.1.1 Causes**

#### **5.1.1.1 Microbiology of the Vagina and the Role of Estrogens**

A wide range of species make up the normal microbiota in vaginal mucosa which varies between pre- and postmenopausal women. In healthy premenopausal women these are generally dominated by *Lactobacillus* species including *L. iners*, *L. crispatus*, *L. gasseri*, *L. jensenii*, followed by *L. acidophilus*, *L. fermentum*, *L. plantarum*, *L. brevis*, *L. casei*, *L. vaginalis*, *L. delbrueckii*, *L. salivarius*, *L. reuteri*, and *L. rhamnosus*.

During the reproductive years, estrogen promotes the growth of lactobacilli by increasing the glycogen content in the vagina and the subsequent processing of this glycogen to glucose within vaginal epithelial cells. This cellular-manufactured glucose serves as nutrient for the lactobacilli allowing them to produce lactic acid which maintains the vaginal environment at an acidic pH (<4.7) protective against bacterial growth, particularly *Prevotella* species and *Gardnerella vaginalis*. High concentrations of estrogen also increase lactobacilli adherence to vaginal epithelial cells in vitro.

With loss of estrogens accompanying menopause come significant local changes in the vagina, marked by thinning and paling of the vagina wall, loss of vaginal elasticity and decreases in normal vaginal secretions. Declining estrogen levels is thought to lead to depletion of lactobacilli, a rise in pH, and increased vaginal colonization with enterobacteria.

Bacterial vaginosis results from changes in the normal local microbiota of the vagina caused by an overgrowth of one or more types of anaerobic bacteria such as *Gardnerella vaginalis*, *Morbillinus* species, *Prevotella* species, *Mycoplasma hominis* and the recently identified *Atopobium vaginae* accompanied by depletion of the protective *Lactobacillus*.

Although the methods by which lactobacilli protect against BV remain unclear they appear to involve the organism's ability to.

- Populate the vaginal epithelium and mucin layer;
- Inhibit pathogen growth and virulence expression;
- Displace pathogens; and
- Modulate host defenses.

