#### 13.1.3.4 Microbiota Analysis

Abundance values will be defined as operational taxonomic units (OTUs). In order to compare microflora diversity, Shannon's diversity index will be calculated for each subject at each treatment phase as the abundance values using OTUs. The Shannon's diversity index ( $S$ ) is

defined as 
$$S = - \sum_{i=1}^{119} p_i \log(p_i)$$
 where  $p_i$  denotes the proportional abundance values at the  $i$ th OTU. The lactobacillus ratio will be calculated for each subject at each treatment phase, as the ratio of total abundance value for the lactobacillus OTUs to the total abundance value for all the OTUs.

To determine if the linear trends in the  $S$  and lactobacillus ratio trajectories differ significantly across subjects and treatment phases, the following linear mixed effect model will be applied to the data  $Y_{it} = \mu + a_i + b_i t + \epsilon_{it}$ . The fixed effect being the intercept only and random effects being subject intercepts and slopes where  $Y_{it}$  denoted the  $S$  value of subject  $i$  at time point  $t$  and  $\mu$  is an unknown fixed constant,  $a_i$  is a random subject intercept,  $b_i$  a random subject slope, and  $a_i$ ,  $b_i$ ,  $\epsilon_{it}$  are independent normal random variables.

In order to determine if a statistical relationship existed between microbial diversity and vaginal symptoms, a weighted least squares analysis will be applied to the data. Severity of vaginal symptoms will be treated as ordinal values 0, 1, 2, and 3, for example. The weighted least

squares model  $\bar{Y}_{id} = \mu_0 + \mu_1 d + \epsilon_{id}$  will be used to test the linear effect of vaginal symptoms with respect to microbial diversity. Where  $\bar{Y}_{id}$  denotes the average  $S$  of subject  $i$  at dryness  $d$ . The quantities  $\mu_0$  and  $\mu_1 d$  are constants representing intercept and slope respectively.

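### Exclusion 8 admits systemic oestrogen users only if they will alter therapy during the study, with no type or timing, which can confound a woman's exploratory comparisons with the always-first no-treatment phase

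*Protocol*

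**What the plan says.** Exclusion 8 reads the same in Protocol section 7.1 and in the synopsis. It excludes women "Currently undergoing local or systemic estrogen therapy who are not willing to alter therapy during the course of the study". Neither place says whether therapy is to be stopped, reduced, started or switched, when this should happen, or whether a stable or washout interval applies.

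Other parts of the Protocol bear on it:

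- **Section 7** rules out exemptions and waivers, so a site has to apply the criterion as written.
- **Exclusion 1 and section 10.3** already bar vaginally applied products, so exclusion 8 in practice concerns systemic oestrogen.
- **Section 10.2** asks that treatment in use on Day 1 be held constant, but only treatment for an intercurrent illness. Oestrogen is not named.
- **Section 5.1.1.1** gives the biological link: "Declining estrogen levels is thought to lead to depletion of lactobacilli, a rise in pH".
- **Section 6** introduces its list with "Subjects will undergo the following treatment phases", and the first item is "Two weeks of no treatment (Days 1-15); followed by". The no-treatment weeks therefore count as one of the phases, and they are never randomised in order.
- **Section 6.2** plans a metabolomic comparison of "differences in the factors associated with improved health between probiotic, placebo, and no treatment conditions" and a microarray comparison of "differences in gene regulation between probiotic, placebo, and no treatment conditions".

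**The concern.** The criterion appears to point the wrong way. A woman on a steady systemic dose who would keep to it is turned away, while one who will change her dose partway through is eligible. The Protocol itself treats oestrogen as a driver of the lactobacilli and pH that the trial measures.

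Randomising the order of probiotic and placebo balances time-related changes between those two conditions on average. It does nothing for a comparison with the no-treatment phase, which comes first in every woman. An oestrogen change after that phase has begun moves with phase, so a shift it causes could be read as an effect of the capsules in that woman's molecular profiles.

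**Working it through.** The Protocol states no figure on this point, so there is nothing to reproduce. The check is a reading of when the change can fall, a count of samples, and a look at which analyses use the no-treatment phase.

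**1. When would the change fall?** Section 8.1 places screening, consent, eligibility review and the first set of samples together at Visit 1, Day 1. Consent must precede any study procedure (sections 8.1 and 15.3). A woman who alters therapy because the criterion asks it of her, and does so while the study is running, would normally do so after her first sample. An earlier change is not forbidden, but nothing requires it.

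**2. Which samples lie on each side?** The synopsis gives the days: "Subjects will provide vaginal samples on Days 1, 5, 15, 19, 26, 36, 40, and 47".

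- No-treatment samples: Days 1, 5, 15 = 3.
- Post-dose samples: Days 19, 26 (first period) and Days 40, 47 (second period) = 4.
- Day 36 is taken before the second dosing and is in neither count.

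| Oestrogen change made | No-treatment samples before it | Post-dose samples before it | Reading |
|---|---|---|---|
| Before Day 1 | 0 of 3 | 0 of 4 | Change separates no samples |
| Just after Day 1 | 1 of 3 | 0 of 4 | Partly aligned with phase |
| Just after Day 15 | 3 of 3 | 0 of 4 | Fully aligned with phase |
| Between Day 26 and Day 40 | 3 of 3 | 2 of 4 | Fully aligned for the second period only |

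The counts treat the effect as immediate. Its speed is not given. If it is slow, a change soon after Day 1 would act more like a later one, and a change shortly before Day 1 could still spill into the study. That is why an interval before Visit 1 is needed.

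**3. What share of the data?** Each woman who alters therapy contributes 1/14 = 7.1% of the within-woman comparisons. The Protocol gives no number of oestrogen users. Assuming 0 to 3 gives 0/14 = 0% to 3/14 = 21.4%.

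**4. Which analyses are exposed?**

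- *Metabolomics* (sections 6.2 and 13.1.3.6): profiles are compared between treatments within a woman, and no treatment is a named condition. Exposed.
- *Microarray* (sections 6.2 and 13.1.3.5): genes are kept if they differ at least 2-fold between phases in an individual. The filter works woman by woman, so one woman's oestrogen change could put genes on the list. Exposed.
- *Diversity and lactobacillus ratio* (section 13.1.3.4): the stated aim is whether the "lactobacillus ratio trajectories differ significantly across subjects and treatment phases", but the model is Y_it = μ + a_i + b_i·t + ε_it. The intercept is the only fixed effect and there is no phase term. An oestrogen change can enter only through that woman's slope b_i (or her residuals); the model estimates no contrast with no treatment.
- *Change in Nugent Score and pH* (sections 13.1.3.1 and 13.1.3.2): baseline is the no-treatment phase, but the planned comparison is between test articles. Only the descriptive summaries are exposed.
- *Primary McNemar test* (section 13.1.2.1): probiotic against placebo in randomised order. A change mainly adds noise.

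**The case against.** The strongest case against runs as follows.

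- **Consequence.** The exposed comparisons are exploratory, in a pilot of 14 women without a sample size calculation, and neither the microarray nor the metabolomic section states a hypothesis test. This stands, and it limits the severity.
- **Safeguards.** A Nugent Score of 4 to 6 is required again at Visit 3 before randomisation and at Visit 6 before the second dosing, and concomitant medication is reviewed at every visit from Day 1 to Day 47. A large early drift would therefore stop dosing, and a reported change would be on record. These reduce the problem. They do not catch shifts inside 4 to 6, changes made after Day 15, or changes in gene expression or metabolites that leave the score alone.
- **Time effects in general.** Because no treatment always comes first, those contrasts are open to any trend over time, with or without oestrogen. This is true, and rewording exclusion 8 would not remove it. The criterion nevertheless adds an avoidable source of such a trend.
- **Intent.** Exclusion 8 may mean that women should come off oestrogen, which would suit the aim in section 5.2 of studying women with depleted lactobacilli. It may equally be a slip for willingness not to alter therapy. The text settles neither, and under the first reading the timing is still missing.

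A reader might infer that the primary comparison is biased, or that the lactobacillus-ratio analysis contains a confounded contrast with no treatment. The documents support neither: order is randomised for the first, and the second has no phase term.

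**Conclusion.** The point holds as a minor one. Followed as written, exclusion 8 brings in systemic oestrogen users on condition that they change therapy during the study, and so normally after the first no-treatment sample. Section 10.2 does not repair this: either it does not reach oestrogen, or it contradicts the criterion.

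For a woman who makes such a change, the exploratory metabolomic and microarray comparisons with no treatment can be confounded, from partly (change just after Day 1) to fully (change just after Day 15). Nothing in the Protocol points to the Day 15 case in particular, so full confounding should not be taken as the expected outcome.

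The size cannot be given. It depends on the number of oestrogen users, when they change, and how fast the change acts, none of which the Protocol states. Section 5.1.1.1 describes the loss of oestrogen at menopause; it does not say that altering systemic therapy shifts the flora within 47 days. If no users enrol, the effect is zero.

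**What to change.** Reword exclusion 8 in section 7.1 and in the synopsis so that any alteration of systemic oestrogen, for example stopping it, is complete for a stated interval before Visit 1, with no further change through Day 47. The sponsor should confirm the interval. Exclusions 1 and 5 use 3 months for vaginal products and oral probiotics, but those windows were not set for oestrogen. In section 10.2, name oestrogen as therapy to be kept constant, so that the two sections agree.

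Whether women on stable, unchanged oestrogen may enter is a separate decision for the sponsor. The current text excludes them, and admitting them would widen the study population, so this fix does not presuppose it.

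The cost is a few sentences in three places, and a few women who would have changed therapy mid-study are delayed or lost.
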